### Intervention

Individuals allocated to the intervention group will in addition to the usual care group receive a comprehensive tailored rehabilitation intervention focusing on supporting RTW.

The intervention is based on a multidisciplinary rehabilitation team approach (psychologists, physiotherapists, social workers, physicians within social medicine and occupational medicine, and psychiatrists). A comprehensive neurocognitive assessment and a thorough individual assessment of rehabilitation needs will be conducted to inform the individually tailored intervention plan. The plan will be developed, discussed, and planned at multidisciplinary rehabilitation team conferences. Ongoing monthly evaluation and possible adjustments of the rehabilitation plan are further discussed at multidisciplinary rehabilitation team conferences. The intervention is designed as a pragmatic individually tailored rehabilitation intervention; hence, the content and the delivery of the rehabilitation will not be uniform but based on individual needs. Therefore, based on the individual rehabilitation plan, a participant can be offered interventions that target the individual needs without limitations in relation to frequency and intensity but with a limit in relation to duration (up until 12 months after the cardiac arrest). Core intervention elements are as follows: (1) comprehensive assessment of individual rehabilitation needs including neuropsychology tests in order to make an individually tailored intervention plan coordinated with the multidisciplinary rehabilitation team; (2) providing strategies to lessen impact for the individual cognitive impairment; (3) educating survivors and relatives about the impact of a cardiac arrest and consequences on daily life; (4) work preparation, including establishment of routines and opportunities to practice work skills; (5) collaboration with the local municipality’s job centre and employers to plan, support, and monitor graded RTW; and (6) short-term therapy by psychologist dealing with thoughts and behaviour in relation to cardiac arrest. Core elements and reference activities in the intervention related to timing are presented in Fig. 1.

**Fig. 1 Fig1:**
[figure not shown]
Core elements and reference activities in the intervention. In addition to the usual care, the pragmatic individual tailored rehabilitation intervention can be delivered for up to 52 weeks

The complex pragmatic intervention is based on a multidisciplinary rehabilitation team approach and developed from a bio-psychosocial model perspective. The intervention is based on the principles from the individual placement and support [13] and stepped care [14] graded exercise therapy [15, 16] and cognitive behavioural therapy [17]. Individual placement and support is a model within rehabilitation focusing on RTW, where the goal is to provide professional services to help people with disabilities participate in the competitive labour market [18]. Stepped care is a system used to monitor and deliver the most effective treatment with the lease resources [14]. Graded exercise therapy is a behavioural treatment programme characterized by graded activity, time contingency, and operant conditioning. The primary aim of this rehabilitation programme is to increase the survivors’ ability to perform their own preferred activities during daily life at home or at work [15, 16]. Cognitive behavioural therapy is a short-term, goal-oriented psychotherapy treatment that takes a hands-on, practical approach to problem-solving [19].

### Usual care

All participants including those allocated to the usual care group will be seen by an occupational therapist if their MoCA screening score ≤ 26. Furthermore, if considered relevant by the discharging unit, survivors are referred for rehabilitation provided and delivered in the local municipality where the participant is resident. The content of the rehabilitation will typically be based on the content of the rehabilitation plan from the discharging hospital unit and an individual assessment of the survivors’ expressed needs, within the local municipality where the participant is resident.

### Feasibility

Each year, around 200 OHCA survivors are discharged from Copenhagen University Hospital-Rigshospitalet and Copenhagen University Hospital-Herlev & Gentofte hospitals. Approximately, 40% of these are part of the labour marked. To our knowledge, this present study will be the first randomized trial worldwide that investigates the effectiveness of a complex multidisciplinary individual tailored rehabilitation intervention targeted RTW in an OHCA population [10]. The feasibility of the intervention was tested on 10 participants. The intervention was found to be relevant and acceptable, as it was feasible to recruit and retain participants despite the COVID-19 pandemic (unpublished data). A few changes have been made to the intervention based on the feasibility testing, for example all participants allocated to the intervention will now have a comprehensive neurocognitive assessment and a thorough individual assessment of rehabilitation needs before the rehabilitation plan is discussed by the multidisciplinary rehabilitation team. Furthermore, to support the patients, the relatives can, if relevant, be offered psychological consultations either alone or with the patients.

### Outcomes

#### Primary outcome

Data for the primary outcome will be obtained from the national register on social transfer payments (DREAM) [20]. The DREAM register is a prospective register based on data from the Ministry of Employment, the Danish Education Registers, the Danish Civil Registration System (CPR registry), and the Danish Tax Authority. The register contains all citizens in Denmark, who have received one or more social transfer payments in the period from 1991 until today. The type of transfer payment is registered on a weekly basis, and the register is updated monthly.

The primary outcome of the clinical trial is labour market participation, defined as a dichotomized outcome, employment vs. on social transfer payment 12 months after hospital discharge.

This measure has been proposed as adequate and relevant measure for assessing employment prognosis following intervention on a similar group of patients [21]. Furthermore, data will be obtained by questionnaire on the degree of workload and comparable work tasks compared to pre-cardiac arrest. Hence, labour market participation 12 months after hospital discharge (employment vs. social transfer benefits (DREAM)) and labour market participation during the 12 months after hospital discharge (DREAM) will be analysed.

Sequence analysis and a multistate model analysis will be used to visualize how survivors change states during the follow-up time and to assess influences from covariates on transitions between stages.

### Secondary outcomes

All secondary outcomes: readiness for return-to-work (RRTW), Multidimensional Fatigue Inventory (MFI-20), The 5-level EuroQol 5-domain (EQ-5D-5L) quality-of-life questionnaire, European quality-of-life survey (HeartQoL), the Pittsburgh Sleep Quality Index (PSQI), Health Literacy Questionnaire (HLQ), and Impact of Event Scale-Revised (IES-R), modified job descriptions and job task, and adverse events will be collected within the first 12 weeks after hospital discharge. There will be at least one interim test at 26 weeks and again at the primary end point at 52 weeks. Please see assessment timeline in Table 1.

**Table 1 Tab1:**
[figure not shown]
SPIRIT figure. Schedule of enrolment, allocation, interventions, and assessments

*t*_1_ 2 weeks, *t*_2_ 6 weeks, *t*_3_ 12 weeks, *t*_4_ 26 weeks, *t*_x_ 52 weeks (primary endpoint). Readiness for return to work (*RRTW*), Multidimensional Fatigue Inventory (*MFI-20*), the 5-level EuroQol-5 domain (EQ-5D-5L) quality-of-life questionnaire, European quality-of-life survey (HeartQoL), the Pittsburgh Sleep Quality Index (PSQI), Health Literacy Questionnaire (HLQ), and Impact of Event Scale-Revised (IES-R). Intervention group only. Sequence analysis of labour market trajectories using data registered in the DREAM database. Only participants allocated to the intervention, §¤list of tests; Trail making A, Trail Making B, digit span forwards, digit span backwards, RBANS list learning, RBANS story memory, Rey’s complex figure test — copy, coding, Rey’s complex figure test, immediate recall, letter number sequencing, design fluency, RBANS list recall, RBANS list recognition, RBANS memory recall, block design, verbal fluency Test (animals), verbal fluency test (S-words)

#### Readiness for return-to-work

This 22-item scale assesses the stage of readiness for return-to-work. Confirmatory factor analyses had satisfactory fit indices to confirm the initial model [22]. The scales form six subscales of precontemplation (three items) and contemplation (three items), prepared for action self-evaluative (four items), and prepared for action behaviour (three items) for participants on full-time sick leave and the stages of uncertain (five items) and proactive maintenance (four items) for participants who are working part time or full time.

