### Secondary outcomes

Secondary outcomes will be analysed using generalized linear mixed-effects models. Data are measured repeatedly, but outcomes are binary or on ordinal scale. Crude and adjusted analysis will be presented. Covariates that will be adjusted for include age at OHCA, sex, educational level, and marital status. Continuous data will be analysed using *t*-test for normally distributed data and Wilcoxon’s signed-rank test for non-normally distributed data. For categorical data, chi-square test will be used.

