### Methods used for assumptions to be checked for statistical methods

In logistic regression, the linearity of log odds for each quantitative variable will be assessed by residual plots. Cooks distance and dfbeta values will be used to assess influential observations. In multistate models, the Markov assumption (previous states do not influence next transition) will be tested using the log-rank-based test [45].

The assumption of time homogeneity (that time spent in a state does not influence next transition) will be assessed using Schoenfeld residuals and by fitting a time homogeneity model and a piecewise constant model and comparing these using a likelihood ratio test. Repeated measures to identify the optimal covariance structure, models with compound symmetry, unstructured covariance, and auto-regressive with heterogeneous variance will be built and compared with ANOVA. The model with the lowest AIC and smallest −2 log likelihood score will be fitted as the final model. Time points should be equally spaced, as survivors fill surveys at approximate times during the study period. Normality will be assessed with a histogram of the residuals. Homoscedasticity will be assessed by plotting fitted values vs. residuals. Influential data points are not likely, as values are defined by surveys. The final model will be adjusted for values at baseline, to take individual variation into account.

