### Planned reporting

Participant’s characteristics are planned to be reported as outlined in Supplemental Table 2. The primary outcome will be reported as unadjusted and adjusted OR of RTW at 12 months (see Table 2). The multistate model will be reported as outlined in Table 5 and visualized using sequence analysis (see Table 3).

**Table 2 Tab2:** Unadjusted and adjusted OR of RTW at 12 months. Odds ratio (OR), 95% confidence interval (95% CI)

	Unadjusted OR RTW (95% CI)	Adjusted OR RTW (95% CI)
Intervention	OR (95% CI)	OR (95% CI)
Age	OR (95% CI)	OR (95% CI)
Male sex	OR (95% CI)	OR (95% CI)
Marital status	OR (95% CI)	OR (95% CI)
Occupation	OR (95% CI)	OR (95% CI)

**Table 3 Tab3:** Unadjusted and adjusted hazard ratio (HR) of RTW at 12 months. 95% confidence interval (95% CI). May include estimates from transient intensity matrix/HR from multistate models

	Unadjusted HR sick leave: full time (95% *CI*)	Adjusted HR sick leave: full time (95% *CI*)	Unadjusted HR sick leave: part time (95% *CI*)	Adjusted HR sick leave: part time (95% *CI*)
Intervention	HR (95% CI)	HR (95% CI)	HR (95% CI)	HR (95% CI)
Age	HR (95% CI)	HR (95% CI)	HR (95% CI)	HR (95% CI)
Sex	HR (95% CI)	HR (95% CI)	HR (95% CI)	HR (95% CI)
Marital status	HR (95% CI)	HR (95% CI)	HR (95% CI)	HR (95% CI)
Occupation	HR (95% CI)	HR (95% CI)	HR (95% CI)	HR (95% CI)
	Unadjusted HR part time: retired (95% *CI*)	Adjusted HR part time: retired (95% *CI*)	Unadjusted HR full time: retired (95% *CI*)	Adjusted HR full time: retired (95% *CI*)
Intervention	HR (95% CI)	HR (95% CI)	HR (95% CI)	HR (95% CI)
Age	HR (95% CI)	HR (95% CI)	HR (95% CI)	HR (95% CI)
Sex	HR (95% CI)	HR (95% CI)	HR (95% CI)	HR (95% CI)
Marital status	HR (95% CI)	HR (95% CI)	HR (95% CI)	HR (95% CI)
Occupation	HR (95% CI)	HR (95% CI)	HR (95% CI)	HR (95% CI)

Unadjusted and adjusted estimates for secondary end points will be reported as outlined in Supplemental Table 3. RTW at 6 months will be assessed with logistic regression, other variables with generalised linear mixed models. Results for PROMs will be reported for each subscale separately in text.

Furthermore, patient-reported RTW, the degree of RTW in hours weekly compared to prior to the cardiac arrest), changed job description, and modification in job task will be reported descriptively.

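### Each readiness-for-return-to-work subscale applies to only one work status, so subscale contrasts between arms at follow-up are made in subsets selected after randomisation and can be biased

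*Protocol article*

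**What the plan says.** The *Readiness for return-to-work* section introduces the instrument as follows: "This 22-item scale assesses the stage of readiness for return-to-work". It lists precontemplation, contemplation, prepared for action self-evaluative and "prepared for action behaviour (three items) for participants on full-time sick leave". The remaining two subscales are "the stages of uncertain (five items) and proactive maintenance (four items) for participants who are working part time or full time".

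RRTW is a named secondary outcome, first collected within 12 weeks of discharge. On later visits, *Secondary outcomes* (under *Outcomes*) states: "There will be at least one interim test at 26 weeks and again at the primary end point at 52 weeks".

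Three statements govern the analysis:
- *Secondary outcomes* (statistical methods): "Secondary outcomes will be analysed using generalized linear mixed-effects models", with crude and adjusted results.
- *Methods used for assumptions to be checked for statistical methods*: "The final model will be adjusted for values at baseline, to take individual variation into account".
- *Planned reporting*: unadjusted and adjusted estimates for secondary end points, and "Results for PROMs will be reported for each subscale separately in text".

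The primary outcome is "employment vs. on social transfer payment 12 months after hospital discharge".

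**The concern.** A participant's work status on the day of the assessment decides which RRTW subscales exist for that participant. Work status arises after randomisation and is what the intervention is meant to alter. A comparison of arms on a sick-leave subscale sets controls still on full-time sick leave against intervention participants still on full-time sick leave, and these need not be comparable groups. If the intervention helps people back to work and the readier ones go first, those left on sick leave in the intervention arm are on average less ready. The additional returners are also, on average, less ready than those who would have worked anyway, so they pull down the mean of the working group. A difference between arms can then appear although nobody's readiness was harmed, or a real gain can be hidden.

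**Working it through.** **Structure of the instrument.** Sick-leave subscales: 3 + 3 + 4 + 3 = 13 items. Working subscales: 5 + 4 = 9 items. 13 + 9 = 22, the stated total, so no item or subscale is common to the two groups.

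**Inputs from *Sample size*.** Control return-to-work rate 71%. Intervention rate 0.71 × 1.25 = 0.8875, given as 88.8%. Analysed number 85 per arm, which reproduces the recruitment target: 85 / (1 - 0.20) = 106.25, rounded up to 107. The 85 serves here only to turn rates into counts.

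**Expected numbers per form at 52 weeks**, treating every non-returner as on full-time sick leave (an assumption):
- Sick-leave form: 85 × 0.29 = 24.65 controls and 85 × 0.112 = 9.52 intervention participants, about 25 and 10.
- Working form: 85 × 0.71 = 60.35 and 85 × 0.888 = 75.48, about 60 and 75.

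**Selection model (assumed).** Work propensity is standard normal. A participant works if it exceeds a threshold c, and the intervention only lowers c. Readiness has correlation ρ with work propensity, and the intervention has no direct effect on it. With p the proportion working, c = Φ⁻¹(1 - p), and mean readiness in SD units is
- working: ρ × φ(c) / p
- sick leave: -ρ × φ(c) / (1 - p)

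The densities are φ(c) = 0.3423 for p = 0.71 and 0.1905 for p = 0.888. Before multiplying by ρ:
- Sick leave: control -0.3423/0.29 = -1.18; intervention -0.1905/0.112 = -1.70; difference -0.52.
- Working: control 0.3423/0.71 = 0.482; intervention 0.1905/0.888 = 0.215; difference -0.27.

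The documents do not give ρ, so a range is shown:

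| ρ | Sick leave, intervention minus control | Working, intervention minus control |
|---|---|---|
| 0.3 | -0.16 SD | -0.08 SD |
| 0.5 | -0.26 SD | -0.13 SD |
| 0.7 | -0.36 SD | -0.19 SD |

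**With a true gain of 0.2 SD for everyone**, 0.2 is added to each entry. The sick-leave difference becomes -0.06 SD (ρ = 0.5) or -0.16 SD (ρ = 0.7). The working difference becomes +0.07 or +0.01 SD. Neither recovers the true 0.2.

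**Whether the planned methods repair this.** A participant on full-time sick leave at the first assessment who later works has no baseline value on the working subscales and no follow-up value on the sick-leave subscales. That participant, whose return to work is the aim of the trial, cannot enter a baseline-adjusted comparison on any subscale. The values are undefined, not unobserved, so the multiple imputation that *Missing data and robustness* allows as a sensitivity analysis has nothing meaningful to fill in.

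**The case against.** **The article may not fix this analysis.** No sentence specifies a between-arm test of each RRTW subscale. The mixed-model statement is generic, the reporting sentence covers all patient-reported measures, the supplementary table for secondary end points is not shown, and a full analysis plan is promised. An analysis of an ordered stage would be compatible with the text. It is true that nothing is spelled out for RRTW in particular. However, the article does commit secondary end points to unadjusted and adjusted estimates and patient-reported results to separate subscales, for an instrument that it describes as split by work status. The problem follows from those statements together, not from missing detail.

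**A reader might infer that the contrast conditions on the primary outcome itself.** The documents do not support this. RRTW separates full-time sick leave from part- or full-time work, whereas the primary outcome separates employment from transfer payment in the DREAM register. The statistical section also recognises private retirement, unemployment without transfer payment, and death. The two splits are close but not the same, and at 26 weeks the conditioning is on an earlier work status. For the same reason the 25 and 10 on sick leave are upper bounds at the planned rates.

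**A reader might also infer that a beneficial intervention will look harmful on both forms, by as much as -0.52 and -0.27 SD.** Those values need ρ = 1 and no effect on readiness, although the intervention includes work preparation and psychological therapy. With a 0.2 SD true gain the working contrast is slightly positive. Sampling error is also large: roughly √(1/25 + 1/10) = 0.37 SD on the sick-leave form and √(1/60 + 1/75) = 0.17 SD on the working form. At ρ = 0.5 both biases are below one standard error, and at ρ = 0.7 they are about one. An inconclusive result is more likely than an apparent harm. This limits the consequence but does not make the contrast interpretable.

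**Conclusion.** The concern holds in limited form. As written, the plan compares arms on each RRTW subscale within a subset defined by work status after randomisation, and such a contrast can be biased. Under the planned rates, all non-returners on full-time sick leave, no direct effect on readiness and ρ between 0.3 and 0.7, the spurious difference is about -0.16 to -0.36 SD among those on sick leave and -0.08 to -0.19 SD among those working. These figures are for readiness; on any subscale where a high score means low readiness, the sign reverses. The size rests on an assumed correlation, and a true gain offsets part of it, so the documents support the statement that the contrasts can mislead, not that they will. RRTW is one of several secondary outcomes, and neither the primary analysis nor the superiority claim depends on it.

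**What to change.** State in the analysis plan that RRTW subscale scores will be reported descriptively by arm and work status at each visit, with the number completing each form, without between-arm tests or claims of effect. State also that subscales that do not apply are undefined and will not be imputed.

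Optionally, if the instrument's scoring supports one ordered stage across both forms, prespecify the staging rule, the ranking across forms and the handling of participants who fit neither form (retired, unemployed, deceased). Then compare arms on that stage in the randomised population. The article gives none of these rules, so this cannot be the default. Because the form follows work status, the stage would also largely overlap with return to work, and the report should say so.

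The main change costs a few sentences and no new data. The article promises the full plan before analysis and expects the last visit at the end of 2026. The price is that subscale-level treatment estimates for RRTW are given up.

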#### Multidimensional fatigue inventory

Fatigue is a very commonly reported symptom in sudden cardiac arrest survivors. To measure the level of fatigue, and change over time, the 20-item patient-reported outcome measure MFI-20 was chosen. MFI-20 consist of five fatigue scales covering the following: general fatigue, physical fatigue, reduced activity, reduced motivation, and mental fatigue [23].

#### The 5-level EuroQol-5 domain

The EQ-5D-5L is a generic Health-Related quality-of-life (HRQoL) measurement tool developed as a generic instrument for HRQoL [24, 25]. EQ-5D-5L comprises five dimensions (mobility, self-care, usual activities, pain/discomfort, and anxiety/depression), each of which has five levels (no problems, slight problems, moderate problems, severe problems, or unable to) and a visual analogue scale (EQ VAS) [25]. The EQ VAS records the patient’s self-rated health on a vertical visual analogue scale, where the endpoints are labelled ‘The best health you can imagine’ and ‘The worst health you can imagine’. The EQ-5D-5L has been adapted for Danish [26], but no psychometric evaluation of the Danish version has been published. However, several studies have evaluated the English version and found acceptable psychometric properties for convergent validity and test-retest reliability [27, 28].

#### European quality-of-life survey

To measure disease-specific health-related quality of life, we have chosen the HeartQoL, which development was supported from the European Society of Cardiology and the European Association of Preventive Cardiology [29]. The 14 items patient-reported outcome has been translated into Danish and showed acceptable psychometric properties in cardiac patients following heart valve surgery, ischemic heart disease, and in recipients of implantable cardioverter defibrillator [30–32].

